### Randomisation procedure

Randomisation (1:1) will be conducted in four separate blocks corresponding to each study site: Gothenburg, Karlstad, Stockholm and Malmö. Microsoft Excel will be used for performing the randomisation based on participant identification numbers, with the process managed by an external researcher to ensure objectivity.

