### Sample size calculation

The sample size estimation was conducted using GPower software (V.3.1.9.7). The study’s primary outcome is the between-group difference in change of Mini-BESTest total scores postintervention. Based on Beauchamp *et al*,^62^ a minimal clinically important difference of 4 points was chosen, with a corresponding baseline SD of 6.5 points for the Mini-BESTest in a stroke outpatient cohort. This yields a standardised effect size of Cohen’s d=0.62 with an α error probability of 0.05 and desired power of 80% (1 – β=0.80). GPower indicates that 36 participants per group (72 total) are required to detect the specified effect size. To allow for up to 10% attrition, the total sample size was increased to 80 participants (40 per group).

Given that this is a multicentre trial conducted across four sites, we initially adjusted the sample size as per CONSORT recommendations for non-pharmacological treatments,^63^ to account for potential clustering effects due to differences between sites or instructors. The design effect was calculated by drawing on estimates from multicentre stroke rehabilitation literature, which typically report ICCs ranging from 0.007 to 0.031.^64^ An ICC of 0.01 was conservatively applied, as applying a higher ICC would have led to a larger sample size that was beyond the financial constraints of the current study and would have been unfeasible. Since the intervention will be delivered across four sites, we adjusted for potential clustering using a calculated design effect of 1.17 using the formula [1 + (*n*−1) × ICC], where *n* is the average cluster size and ICC is the intracluster correlation coefficient, which yielded a cluster-adjusted sample size requirement of 84 participants (approximately 21 per site).

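### The design effect of 1.17 rests on 18 participants per site where about 21 are planned, was applied to the total before attrition, and comes from a whole-site formula in a trial that randomises individuals within sites

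*Protocol article*

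**What the plan says.** All the figures are in the Sample size calculation section of the protocol article.

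- Target difference and SD: "a minimal clinically important difference of 4 points was chosen", with a "corresponding baseline SD of 6.5 points".
- Error rates: "d=0.62 with an α error probability of 0.05 and desired power of 80"%. The section does not say whether the test is one- or two-sided.
- Unadjusted size: "36 participants per group (72 total) are required to detect the specified effect size".
- Attrition: "To allow for up to 10% attrition, the total sample size was increased to 80 participants (40 per group").
- Clustering: the total is then adjusted "using a calculated design effect of 1.17", from 1 + (n − 1) × ICC, with n defined as the average cluster size and ICC = 0.01. The result is 84 participants, "approximately 21 per site".

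The section states neither the n that was put into the formula nor the total that was multiplied.

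The Randomisation procedure section says: "Randomisation (1:1) will be conducted in four separate blocks corresponding to each study site". Both arms are therefore present at every site. Only the RGM arm receives group sessions led by a practitioner (Intervention); controls continue their usual activities (Waitlist control group).

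**The concern.** Three things in this paragraph do not fit together. The design effect belongs to a smaller site than the one named in the same sentence. Attrition and clustering are presented as successive steps, yet the final total is only 4 above the attrition-adjusted 80, far less than a 17% inflation of 80 would add. And the formula is the one for trials in which whole sites are allocated to an arm, which this trial does not do.

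The recruitment target of 84 rests on this paragraph. A reader will take it that 84 allows for both 10% attrition and clustering at 80% power, and the paragraph's own numbers do not support that.

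**Working it through.** **Inputs** (all from the Sample size calculation section): 72 unadjusted, 80 after attrition, 4 sites, ICC 0.01, design effect 1.17, total 84, about 21 per site.

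**1. Reproducing the plan's figure.**
- Setting 1 + (n − 1) × 0.01 = 1.17 gives n = 18, which is 72/4.
- 72 × 1.17 = 84.24, reported as 84.

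So 84 does follow from the formula, with 18 per site and a base of 72.

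**2. Using the stated site size.**
- 1 + (21 − 1) × 0.01 = 1.20.
- 72 × 1.20 = 86.4, so 87, or 88 for equal arms.
- 84/1.20 = 70 effective participants, against 72.
- Solving N = 72 × [1 + (N/4 − 1) × 0.01] gives 86.9, the same answer.

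The difference from 84 is 3 to 4 participants.

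**3. Keeping the attrition allowance.**
- 80 × 1.17 = 93.6, so 94.
- 80 × 1.20 = 96.
- Looking at it from the other side, 84 × 0.9 = 75.6 remain, or 18.9 per site. The design effect is then 1 + 17.9 × 0.01 = 1.179, and 75.6/1.179 = 64.1 effective participants. With 1.17 it is 64.6.

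Either way the effective size is about 64 to 65, against 72.

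**4. Clustering in the RGM arm only.** Assume one training group per site. The article does not give the group size.
- Group size: 42/4 = 10.5.
- Inflation in the RGM arm: 1 + (10.5 − 1) × 0.01 = 1.095.
- Average over the two arms: (1.095 + 1)/2 = 1.0475, about 1.05.
- 72 × 1.05 = 75.6, and 80 × 1.05 = 84.
- After attrition, 75.6/1.05 = 72 effective participants.

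**5. Power** (two-sample t test, two-sided 0.05, d = 0.62).

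| Case | Effective total | Power |
|---|---|---|
| Plan's 36 per arm | 72 | 73.7% |
| 84 at 1.20, no attrition | 70 | 72.5% |
| 84 less 10%, at 1.179 | 64.1 | 68.6% |
| 84 less 10%, at 1.05 | 72.0 | 73.7% |

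The first row is below 80% for a separate reason. At d = 0.62, a two-sided test needs 42 per arm for 80% power and a one-sided test needs 33, so 36 per arm matches neither. That gap is not caused by the clustering step. The part due to 18 versus 21 per site is 73.7% − 72.5% = 1.2 percentage points.

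**The case against.** The strongest reply is that 84 is correct arithmetic: 72/4 = 18, the formula gives 1.17, and the product rounds to 84. This stands. A reader might infer from the mismatch of 18 and 21 that 84 is not what the formula gives, or that the mismatch by itself leaves the trial seriously short. The document supports neither. The cited ICC range of 0.007 to 0.031 gives design effects of 1.14 to 1.62 at 21 per site, and totals of about 82 to 117 on a base of 72, so 3 to 4 participants are well inside the uncertainty of the input.

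It can also be said that 18 is close to the site size left after attrition (18.9). That is true, but it does not rescue the total. On that reading the 75.6 who remain must be divided by about 1.18, which gives 64.

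A third reply is that two of the criticisms pull in opposite directions. Correcting the site size and the base raises the requirement, while replacing the whole-site formula lowers it. This also stands, and it means that a plain statement that 84 is too few would go too far. The shortfall of 64 against 72 holds under the plan's own formula. Under clustering in the RGM arm only, 84 yields about 72 after attrition. That result depends on one group per site and an ICC of 0.01. It also leaves out any variation of the treatment effect between sites, and the article names both sites and instructors as sources of clustering.

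**Conclusion.** The point holds, with limits. The design effect does not match the site size given beside it, which is a small error of 3 to 4 participants. The step that produced 84 replaced the attrition allowance instead of adding to it; by the plan's own method the total would be about 94 to 96, and 84 enrolled is worth about 64 participants against 72. The formula itself does not fit individual randomisation within sites, and a better-fitting one is likely to give a smaller inflation, about 1.05 under the assumptions above.

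Whether 84 falls short of 72 effective participants therefore depends on the clustering model, which the plan must choose. Under neither model does the paragraph show 80% power with a two-sided test at d = 0.62: after 10% attrition the figures are about 69% with the plan's formula and about 74% with RGM-arm clustering. Most of the distance from 80% comes from the separate discrepancy in the 36 per group.

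**What to change.** Keep 84 and rewrite the paragraph.

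1. State the cluster size n and the total that was multiplied.
2. Choose one clustering model. One option is the plan's formula at the actual site size. The preferable option is clustering in the RGM arm only, with the planned training-group size stated and site added as a factor in the analysis model; the Quantitative data analysis section names only time and group as factors.
3. Restate the design effect under that model, and the power that 84 gives after 10% attrition, with the sidedness of the test.
4. Do not state or imply that 84 covers both clustering and attrition at 80% power.

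The two options move the requirement in opposite directions, so they should not be mixed. The cost is one rewritten paragraph, one added model term under the preferred option, and a less favourable power statement. No extra participants are needed.

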### Quantitative data analysis

All quantitative data will be analysed using both descriptive and inferential statistical methods. Prior to conducting hypothesis testing, data will be assessed for completeness, normality and the presence of outliers. The distribution of continuous variables will be evaluated using visual inspection and the Shapiro-Wilk test to determine the suitability of parametric or non-parametric analyses. Baseline characteristics between the intervention and control groups will be compared using Mann-Whitney U tests for continuous variables and χ^2^ tests for nominal variables to assess group equivalence. All analyses will follow the intention-to-treat principle, meaning that all participants will be analysed in the groups to which they were originally randomised, regardless of adherence or dropout. Any missing data will be managed using appropriate imputation strategies, depending on the pattern and mechanism of missingness. The effects of the intervention on primary and secondary outcomes will be examined using mixed-model repeated measures ANOVA (analysis of variance) or appropriate non-parametric alternatives, with time (baseline, postintervention, 3-month follow-up) and group (RGM vs control) as factors.

To address multiplicity in the analysis of the 13 secondary outcomes (FES-I, Memory Test, Victoria Stroop Test, Rey Complex Figure Test, SPPB, 10MWT, 6MWT, ODTA, 9HPT, SIS-16, MADRS, RAND-36 and EQ-5D-5L), the Benjamini-Hochberg False Discovery Rate (FDR) procedure will be applied to control the expected proportion of false positives. Effect sizes of the variables will be expressed using partial eta squared. All statistical analyses will be conducted using IBM SPSS Statistics (V.29.0.1), with the FDR procedure implemented using the SPSS syntax. A significance level of p<0.05 will be applied for the primary outcome, while FDR-adjusted p values will be used for secondary outcomes.

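### A normality check on the outcome data chooses between repeated-measures ANOVA and an unnamed non-parametric test for the primary outcome, so the primary test and effect measure are not fixed in advance

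*Protocol article*

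**What the plan says.** All of the analysis text is in the Protocol article, section Quantitative data analysis.

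- Timing: "Prior to conducting hypothesis testing, data will be assessed for completeness, normality and the presence of outliers".
- Decision rule: the continuous variables are examined by "visual inspection and the Shapiro-Wilk test to determine the suitability of parametric or non-parametric analyses". No threshold is given. Nothing says what happens if the plot and the test disagree, or whether raw scores, change scores or individual arms and visits are examined.
- Scope: "The effects of the intervention on primary and secondary outcomes will be examined using mixed-model repeated measures ANOVA", and the sentence continues "or appropriate non-parametric alternatives, with time (baseline, postintervention, 3-month follow-up) and group (RGM vs control) as factors". The switch therefore covers the primary outcome as well as the secondary ones.
- Effect measure: "Effect sizes of the variables will be expressed using partial eta squared".

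The Sample size calculation section says what the trial is meant to estimate: "The study’s primary outcome is the between-group difference in change of Mini-BESTest total scores postintervention". It takes 4 points as the minimal clinically important difference and 6.5 points as the SD.

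**The concern.** A primary analysis should be fixed before outcome data are seen. Here the data choose between two routes, and only one of them is identified.

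Two features make this more than a matter of style. First, the normality assumption of a linear model concerns its residuals. The shape of a raw variable is weak evidence about them, and with about 40 people per arm a comparison of means tolerates moderate non-normality. The check can therefore discard a sound analysis. Second, the routes need not answer the same question. The trial is sized on a mean difference in change, in points. A rank test addresses a shift in ranks and does not by itself give an adjusted mean difference. The only effect size named, partial eta squared, belongs to the ANOVA route, so none is specified if the switch is made.

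At stake are the meaning of the primary result and, depending on which fallback is picked, a good part of the power.

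**Working it through.** **Inputs from the article.** Difference 4 points; SD 6.5; alpha 0.05 (taken as two-sided); 84 randomised 1:1; attrition up to 10%. Analysed per arm: 84 × 0.9 / 2 = 37.8, so 38.

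**Assumptions not in the article.** Normal scores, the same SD at both visits, and a pre-post correlation r of 0.5, 0.7 or 0.8.

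**The article's own figure.** 4 / 6.5 = 0.615, which agrees with its d = 0.62. Its 36 per group does not follow from a two-sided t-test at 80% power (42 to 43 per group). That is a separate matter and is not used here.

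**Step 1: power of each possible primary test.**
- t-test of change: SD of change = 6.5 × √(2(1 − r)), which is 6.50, 5.03 and 4.11 at the three correlations. So d = 4 / SD = 0.615, 0.794 and 0.973.
- Rank test (Mann-Whitney) of change: same d, with effective n = 38 × 3/π = 36.3 per arm.
- Rank test of week-12 scores only: d = 0.615 at every r, effective n = 36.3.
- ANCOVA on baseline: residual SD = 6.5 × √(1 − r²) = 5.63, 4.64 and 3.90.

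| Test | r = 0.5 | r = 0.7 | r = 0.8 |
|---|---|---|---|
| t-test of change | 75.4% | 92.8% | 98.7% |
| Ranked change | 73.4% | 91.6% | 98.3% |
| Ranked week-12 score | 73.4% | 73.4% | 73.4% |
| ANCOVA | 86% | 96% | 99% |

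Loss against the t-test of change: if change is ranked, 75.4 − 73.4 = 2.0, then 1.2 and 0.4 points. If only week-12 scores are ranked, 2.0, 19.4 and 25.3 points. Simulation of 20,000 trials per correlation gave losses of 2.6, 1.4 and 0.4 points, and of 2.5, 19.6 and 25.9 points. Rounded, the ranges are 0 to 3 and 2 to 26. The lower end of the second range is sensitive to simulation error: with 3,000 trials the standard error of one power estimate is √(0.75 × 0.25 / 3000) = 0.8 points, so a short run can show 4.

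**Step 2: how often chance alone triggers a switch.** Take exactly normal data and Shapiro-Wilk at 0.05, with any rejection forcing the switch.
- Week-12 change tested in each arm (two tests): 1 − 0.95² = 9.8%; simulated 9% to 10%.
- Each arm at each visit (six tests): 1 − 0.95⁶ = 26.5% if independent; simulated 24% to 27% with correlated visits.

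The article fixes neither the number of tests nor the variable, so the rate cannot be narrowed further.

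**Step 3: type I error.** This was simulated with 36 per arm, r = 0.8, and scores rounded and bounded at 0 and 28 (the bounds are an assumption; the article gives the item count but no score range). Over latent means of 16 to 24, the two-stage procedure rejected a true null in about 4.6% to 5.4% of trials, whether the fallback ranked change or week-12 scores. With a true 4-point effect, the t-test of change and the rank test of week-12 scores disagreed in about 28% to 37% of trials.

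**The case against.** The strongest reply is that this is a condensed article and that a switching criterion and a named rank test belong in an analysis plan that is not shown. That is fair for the missing threshold. It does not answer the main point: the article states a data-driven choice as its method, and an analysis plan that followed it would still let the data choose.

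Other replies stand and limit the point.

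- A reader might infer that Shapiro-Wilk alone decides. The text joins visual inspection to it and writes no p-value trigger.
- A reader might infer that the fallback must lose the group-by-time contrast. The article never names Mann-Whitney or Friedman as the fallback; Mann-Whitney appears only for baseline comparisons. The sentence also keeps time and group as factors. A rank test of change scores, or a rank-based factorial method, would keep the contrast. The supported statement is that the fallback may not keep it.
- A reader might set ANCOVA (86% to 99%) against ranked week-12 scores (about 73%) and call the gap the cost of the switch. Neither test is named in the article for this purpose, and that gap mixes the cost of switching with the gain from baseline adjustment. The t-test of change is the fairer reference.
- The Study design section says that those analysing the data are blinded to allocation. This makes a choice that favours one result less likely, but it does not fix the estimand.

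**Conclusion.** The point holds in a limited form. For the primary outcome, a visual and Shapiro-Wilk check of the variables chooses between repeated-measures ANOVA and an unnamed alternative, so the test and the effect measure are not fixed in advance. The alternative may not test or estimate the 4-point difference in change on which the trial is sized.

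A reader might infer that the false-positive rate is inflated. The calculations do not support that; the two-stage procedure stayed close to 5%. The harm is an unfixed estimand and a possible loss of power. That loss is negligible to small if change is ranked, and large only if the fallback drops the baseline and the pre-post correlation is high. These sizes rest on the assumed normality, equal SDs and correlations of 0.5 to 0.8. The 10% to 26% trigger rate rests on a switching rule that the article does not state. The defect does not make the trial invalid, but it should be corrected before any outcome data are examined.

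**What to change.** Delete the normality-based choice for the primary outcome. In its place:

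1. Name one primary model for the week-12 Mini-BESTest difference, adjusted for baseline and site (ANCOVA, or a linear mixed model with the week-12 contrast stated), to be used whatever the normality result.
2. Report the between-group difference in points with its 95% confidence interval as the primary effect measure.
3. Check model residuals graphically, for description and not for selection.
4. Give a bootstrap or robust-standard-error confidence interval for the same mean difference, labelled as a sensitivity analysis only.

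Under the assumptions above, ANCOVA has 86% to 99% power at 38 per arm, at least as much as any route the present wording could lead to among those checked. The cost is a change of wording and one additional sensitivity analysis. Recruitment, visits and data collection are unchanged.

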### Outcomes

The periods when the outcome measures would be assessed are illustrated in table 1.

**Table 1 T1:** Schedule of outcome assessments for the Ronnie Gardiner Method intervention.

Outcome measures	Baseline (Week 0)	Post-intervention (Week 12)	Follow-up (Week 24)
Primary outcome measure			
Mini-BESTest	x	x	x
Secondary outcome measures			
FES-I	x	x	x
Memory test (Immediate & Delayed Recall)	x	x	x
Victoria Stroop Test	x	x	x
Rev Complex Figure Test	x	x	x
SPPB	x	x	x
10MWT	x	x	x
6MWT	x	x	x
ODTA	x	x	x
9HPT	x	x	x
SIS-16	x	x	x
MADRS	x	x	x
RAND-36	x	x	x
EQ-5D-5L	x	x	x
Other pre-specified outcome measures			
MoCA	x		
PACES		x	
Focus Group Interviews		x	
Intervention-related costs	x	x	x

EQ-5D-5L, EuroQol 5-Dimension 5-Level; FES-I, Falls Efficacy Scale–International; 9HPT, 9-Hole Peg Test; MADRS, Montgomery–Åsberg Depression Rating Scale; Mini, BESTest, Mini–Balance Evaluation Systems Test; MoCA, Montreal Cognitive Assessment; 6MWT, 6-Minute Walk Test; 10MWT, 10-Meter Walk Test; ODTA, Observational Drinking Task Assessment; PACES, Physical Activity Enjoyment Scale; SIS-16, Stroke Impact Scale–16; SPPB, Short Physical Performance Battery.

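### The primary outcome is a week-12 difference in Mini-BESTest change, but the stated three-visit ANOVA with partial eta squared ties the primary p-value and effect size to no week-12 contrast

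*Protocol article*

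**What the plan says.** Under Sample size calculation, the protocol article states that the "primary outcome is the between-group difference in change of Mini-BESTest total scores postintervention". Table 1 under Outcomes puts the post-intervention visit at week 12 and the follow-up at week 24. The trial is sized on this one comparison: "a minimal clinically important difference of 4 points was chosen, with a corresponding baseline SD of 6.5 points".

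Under Quantitative data analysis, one method serves every outcome: "The effects of the intervention on primary and secondary outcomes will be examined using mixed-model repeated measures ANOVA", or a non-parametric alternative, "with time (baseline, postintervention, 3-month follow-up) and group (RGM vs control) as factors". The effect measure follows: "Effect sizes of the variables will be expressed using partial eta squared". The decision rule is: "A significance level of p<0.05 will be applied for the primary outcome". The section does not say which term or contrast of the model this level applies to. It does not mention a week-12 comparison or a mean difference in points.

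**The concern.** The endpoint is one contrast, between two groups, over one interval, in Mini-BESTest points. The analysis is a model with two visits after baseline. Its usual test of a treatment effect on change is the group-by-time interaction, which has 2 degrees of freedom and asks whether the group difference varies anywhere across baseline, week 12 and week 24. That is a different hypothesis from the one the trial was sized for.

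Two things are at stake. First, the primary outcome could be declared positive on a difference that appears only at week 24, with nothing at week 12. Second, the stated effect measure would not answer the clinical question. Partial eta squared is a share of variance: it does not show direction, visit or size in points, so it cannot be compared with the 4-point difference. With no deciding term named, the choice could also be made after the data are seen.

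**Working it through.** **Inputs from the protocol article.** Difference 4 points; SD 6.5 (a baseline SD); alpha 0.05; 1:1 allocation; 84 randomised; 10% attrition.

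**Assumptions, not in the document.** Two-sided testing; SD 6.5 at every visit; equal correlation r between visits (compound symmetry), with r from 0.5 to 0.8.

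**The plan's own figures.** Effect size: 4 / 6.5 = 0.615, which the article gives as 0.62. The 36 per group is not reproduced by a two-sided t-test, which needs 42 to 43; a one-sided t-test needs 33 to 34. That is a separate matter and nothing below depends on it. Analysed number: 84 × 0.9 = 75.6, so n = 38 per arm.

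**Step 1: what the interaction test responds to.** Let δ be the group difference at (baseline, week 12, week 24). The noncentrality of the interaction F test, with 2 and 2(2n − 2) = 148 df, is

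λ = (n/2) × Σ(δ − mean δ)² / [SD² × (1 − r)].

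For δ = (0, 4, 4) the mean is 2.667 and the centred sum of squares is 7.111 + 1.778 + 1.778 = 10.667. The patterns (0, 4, 0), (0, 0, 4) and (0, −4, 0) give the same 10.667.

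- r = 0.5: λ = 19 × 10.667 / 21.125 = 9.6; power 79%.
- r = 0.7: λ = 19 × 10.667 / 12.675 = 16.0; power 95%.
- r = 0.8: λ = 19 × 10.667 / 8.45 = 24.0; power 99%.

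So a sustained benefit, a week-12 benefit that disappears, a benefit seen only at week 24 and a week-12 harm are all equally likely to give p<0.05.

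**Step 2: week 24 alone.** Under (0, 0, 4) the week-12 endpoint is null. The interaction rejects in 79% of trials at r = 0.5 and 95% at r = 0.7. In simulation (4,000 trials per setting) the figures were 78.6% and 95.0%, while a baseline-adjusted week-12 contrast rejected in 4.5% and 5.4%, close to its nominal 5%.

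**Step 3: the effect measure.** Expected partial eta squared is about (λ + 2) / (λ + 2 + 148). At r = 0.5 this is 11.6 / 159.6 = 0.07, and at r = 0.7 it is 18.0 / 166.0 = 0.11. It is the same for all four patterns, including the harm.

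**Step 4: is power lost?** Take δ = (0, 4, x). The centred sum of squares is 16 + x² − (4 + x)²/3, which is smallest at x = 2, where it equals 16 + 4 − 12 = 8. The comparator is a two-sided t-test of change to week 12, whose SD is 6.5 × √(2(1 − r)).

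| r | Interaction, x = 0 or 4 | Interaction, x = 1 or 3 | Interaction, x = 2 | Week-12 change t-test |
|---|---|---|---|---|
| 0.5 | 79% | 70% | 66% | 75% |
| 0.7 | 95% | 90% | 88% | 93% |
| 0.8 | 99% | 98% | 97% | 99% |

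The loss is greatest when the effect halves by week 24: about 9 points at r = 0.5 (75 − 66) and about 5 at r = 0.7 (93 − 88). If the effect is sustained or fades completely, nothing is lost.

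**Step 5: the contrast that fits the endpoint.** Baseline-adjusted, the week-12 SE is 6.5 × √(1 − r²) × √(2/38), which is 1.29, 1.06 and 0.89 at r = 0.5, 0.7 and 0.8. Power for 4 points is 86%, 96% and 99%, and the expected 95% CI half-width is 2.6, 2.1 and 1.8 points.

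**The case against.** The strongest reply is that the analysis section names a model family and its factors, not a deciding test. The word interaction does not appear there. The same model can produce the week-12 contrast, the sample size section already fixes measure, comparison and visit, and contrasts and confidence intervals are often left to an analysis plan, which is not shown here. This stands in part. A reader might infer that the plan cannot test or estimate its endpoint; the document does not support that, and the 2-df interaction is the natural reading rather than a stated term. But the article does more than leave detail out: it fixes the model, the three time levels, the effect measure and the alpha for the primary outcome, and together these do not lead to the endpoint it defines.

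Three other stronger readings also fail.

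- A reader might infer that a real week-12 effect that fades would generally be missed. Step 4 shows otherwise: the loss arises only with partial change between the visits, and complete fading costs nothing.
- A reader might take the group main effect, which averages in the baseline visit, as the primary test. The article does not name it, and a difference in change is an interaction quantity.
- A reader might infer that the mean difference will be withheld. The article is only silent on it.

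Finally, no effect at the end of training followed by 4 points three months later is an extreme pattern, and the article gives no reason to expect it. It shows what the test responds to; it is not a forecast.

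**Conclusion.** The concern holds as a mismatch between endpoint and analysis. Read naturally, the stated primary test can be significant from week 24 alone (about 79% at r = 0.5 and 95% at r = 0.7 under 0 points at week 12 and 4 at week 24), and the stated effect measure cannot be set against the 4-point difference. It is not a general loss of power: against a week-12 change contrast the interaction gives up at most about 9 points over the correlations examined, and none if the effect is sustained or fully lost.

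The percentages rest on 38 analysed per arm, SD 6.5 at all visits, compound symmetry, two-sided testing and the assumed correlations. The mismatch itself rests on none of these, because it follows from comparing the two sections.

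**What to change.** In Quantitative data analysis, name the RGM-minus-control difference in Mini-BESTest change from baseline to week 12, preferably baseline-adjusted, as the single-df primary contrast from the longitudinal model, tested at two-sided 0.05. Make the week-24 difference a secondary contrast. Report the mean difference in points with its 95% CI and interpret it against the 4-point difference. Keep partial eta squared only as a supplement.

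This changes analysis wording only and needs no new data, visits or participants. It should be settled before outcome data are examined by group, because a deciding contrast chosen afterwards is no longer prespecified.

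### Baseline enters the repeated-measures ANOVA as a level of time and not as a covariate, which gives away precision on the week-12 primary contrast

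*Protocol article*

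**What the plan says.** The Quantitative data analysis section names one method for the primary and secondary outcomes: "mixed-model repeated measures ANOVA (analysis of variance) or appropriate non-parametric alternatives, with time (baseline, postintervention, 3-month follow-up") as one factor and group as the other. Baseline is therefore one of three outcome levels, and no covariate is listed. The schedule in Table 1 shows the Mini-BESTest and all 13 secondary measures taken at baseline, at "Post-intervention (Week 12") and at week 24.

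The Sample size calculation section defines the target: "The study’s primary outcome is the between-group difference in change of Mini-BESTest total scores postintervention". It plans on "a minimal clinically important difference of 4 points was chosen, with a corresponding baseline SD of 6.5 points", giving a "standardised effect size of Cohen’s d=0.62 with an α error probability of 0.05 and desired power of 80" per cent. It then reports that "GPower indicates that 36 participants per group (72 total) are required to detect the specified effect size", and that "To allow for up to 10% attrition, the total sample size was increased to 80 participants (40 per group"). A design effect of 1.17 leads to the final 84.

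The Randomisation procedure section allocates separately within each of the four sites.

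**The concern.** When baseline is a free level of the time factor, the model estimates a separate baseline mean for each group. The week-12 treatment contrast is then the week-12 difference minus the observed baseline difference. Under randomisation the expected baseline difference is zero, so subtracting all of it adds noise whenever r is below 1. Conditioning on baseline subtracts only the share that predicts the outcome, and under equal variances it is never less precise.

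The structure has a second effect. Three levels of time give a group-by-time test with 2 degrees of freedom, which asks whether the groups differ in any pattern over the three visits. The primary outcome is a single contrast at one visit, and the section does not say which term or contrast carries the primary conclusion.

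What is at stake is the width of the interval and the power for the primary outcome. The Sample size calculation section says that a larger sample was beyond the budget, so precision that costs nothing is worth having.

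**Working it through.** **The plan's own figure.** 4/6.5 = 0.615, stated as 0.62. A two-sided two-sample t-test at α = 0.05 and 80% power needs 43 per group at d = 0.615 or 42 at d = 0.62. The stated 36 per group is not reproduced: it gives 73–74% two-sided power. The later steps do reproduce arithmetically: 72/0.9 = 80, and 72 × 1.17 = 84.2. These sample-size matters are separate from the present point; they are shown only to fix the inputs.

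**Inputs.** From the Sample size calculation section: difference 4 points, SD 6.5 (a baseline SD), α = 0.05, total 84, attrition 10%. Analysed per arm: 84 × 0.9 / 2 = 37.8, taken as 38. Assumed: a two-sided test (sidedness is not stated), the same SD of 6.5 at both visits, and r, which the document does not give. No clustering term is applied to either method.

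**Formulas.**
- Baseline as a level: SD of change = 6.5 × √(2(1−r)).
- Baseline as a covariate: residual SD = 6.5 × √(1−r²).
- Variance ratio, covariate to change: (1−r²) / (2(1−r)) = (1+r)/2.
- Power: noncentral t with noncentrality 4 / (SD × √(2/38)).

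**Example at r = 0.5.** SD of change = 6.5 × √1 = 6.50; residual SD = 6.5 × √0.75 = 5.63. √(2/38) = 0.229. Noncentrality is 4/(6.50 × 0.229) = 2.68 against 4/(5.63 × 0.229) = 3.10, so power is 75% against 86%.

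**Range of r.**

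| r | SD, change | SD, adjusted | Variance ratio | Power, change | Power, adjusted | n per arm for 80%, change | n per arm for 80%, adjusted |
|---|---|---|---|---|---|---|---|
| 0.3 | 7.69 | 6.20 | 0.65 | 61% | 79% | 60 | 39 |
| 0.5 | 6.50 | 5.63 | 0.75 | 75% | 86% | 43 | 33 |
| 0.6 | 5.81 | 5.20 | 0.80 | 84% | 91% | 35 | 28 |
| 0.7 | 5.03 | 4.64 | 0.85 | 93% | 96% | 26 | 23 |
| 0.8 | 4.11 | 3.90 | 0.90 | 99% | 99% | 18 | 16 |

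The SD of change equals the planning SD of 6.5 only at r = 0.5.

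**The three-level test.** The table describes the week-12 contrast. The 2-df group-by-time F test was simulated separately: 4,000 runs, 38 per arm, a 4-point effect at week 12, equal correlation between all visits.

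| r | Effect at week 24 | Group-by-time (2 df) | Group main effect | Week-12 ANCOVA |
|---|---|---|---|---|
| 0.5 | 4 points | 78% | 60% | 86% |
| 0.5 | 2 points | 66% | 37% | 87% |
| 0.5 | 0 points | 80% | 20% | 86% |
| 0.7 | 4 points | 95% | 51% | 96% |
| 0.7 | 2 points | 87% | 32% | 95% |
| 0.7 | 0 points | 96% | 17% | 96% |

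The power of the 2-df test for a fixed week-12 effect moves with what happens at week 24. The group main effect averages in the baseline visit and is weakest throughout.

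**The case against.** The strongest defence is that nothing here is biased. Under randomisation the change contrast is a valid estimate, and it matches the outcome as the Sample size calculation section words it. That stands, and it limits the point to efficiency. It does not favour the unadjusted contrast, however: once baseline is a covariate, modelling the week-12 value or the change gives the same group coefficient, so the adjusted analysis addresses the same difference.

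It is also fair that the gain depends on an unknown r. At r = 0.8 both methods reach 99% and the gain is negligible; at 0.3 it is 18 percentage points.

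A third defence is that the method's name may mean a likelihood-based mixed model. This would change the handling of incomplete participants but not the loss of precision, because a group-by-time model with baseline as an outcome still gives each group its own baseline mean unless a constraint is added, and none is stated.

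Two stronger readings are tempting. A reader might infer that the ANOVA is a complete-case method and so contradicts the statement "All analyses will follow the intention-to-treat principle, meaning that all participants will be analysed in the groups to which they were originally randomised". The document does not support this. The same section plans imputation of missing values, the Ethics and dissemination section keeps what a participant contributed before withdrawing, and a likelihood-based model would use incomplete participants anyway. Partial eta squared hints at the classical procedure but does not settle it, and the imputation method is a detail that an analysis plan may carry.

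A reader might also infer that this choice leaves the trial short of its stated power. The figures do not show that as a flat fact: change-score power is 84% at r = 0.6 and higher beyond, and is below 80% at r = 0.5 and 0.3.

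**Conclusion.** The point holds as a loss of efficiency. The protocol article fixes baseline as an outcome level for the primary and all secondary outcomes, and thereby gives up a share (1−r)/2 of the variance of the week-12 contrast: 35% at r = 0.3, 25% at 0.5, 15% at 0.7 and 10% at 0.8. In power at 38 per arm this is worth 18, 11, 3 and about 0 percentage points respectively. The sizes rest on equal SDs of 6.5 at both visits, a two-sided test, 10% attrition from 84, and assumed values of r. The lack of focus of the 2-df test on week 12 is a second cost of the same model structure; its size also depends on the week-24 effect. Neither affects validity, and neither shows a breach of intention-to-treat.

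**What to change.** Replace the repeated-measures ANOVA wording with a linear mixed model in which the week-12 and week-24 values are the outcomes. The terms are group, visit, group by visit, the baseline value of the same measure and its interaction with visit, and site, since randomisation is done within site. Name the week-12 group difference, in Mini-BESTest points, as the primary contrast and the week-24 difference as secondary. Use the same model for the continuous secondary outcomes. Such a model uses all available post-baseline data, so a participant seen at week 12 but not at week 24 still contributes.

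The cost is a change of analysis wording, best made before the data are unblinded. SPSS, the software already named, can fit the model, and no extra assessments or participants are needed.
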